## Abstract

Maintaining the ability to walk is one of the significant challenges in people with multiple sclerosis (MS) for keeping a good quality of life as the disease and the aging process progresses. Overground robotic (OR) wearable exoskeletons are promising tools for gait rehabilitation, but currently there is no evidence of their clinical effects on patients with MS. The present study aims to determine the effects of an OR intervention in people with MS and moderate to severe walking disabilities and ascertain if benefits are maintained over a follow-up period of 3 months. This randomized controlled trial will include 36 participants with MS. Inclusion criteria are: older than 18 years, definitive diagnosis of MS, 4.5–7 points on the EDSS (Expanded Disability Status Scale), and needing one or two canes or crutches for walking outdoors. Subjects in the control group will receive conventional physiotherapy sessions at ADEMBI (Asociación de Esclerosis Múltiple de Bizkaia) provided to control spasticity, maintain articular range and exercise balance. Subjects in the intervention group will receive the same physiotherapy but also participate in a progressive OR gait training program assisted by the Ekso^TM^ exoskeleton. The program consists of twice a week individually supervised sessions in two setting modalities: *PreGait* and *ProStepPlus*. The training parameters (duration, speed, cadence, length of steps) will be set during the first session and the progression and intensity of the intervention will be adapted to the tolerance of each participant. The primary outcome of this study is gait speed. Secondary outcomes will include physical and cognitive performance tests, clinical, fatigue and quality of life assessments, and changes in the plasma levels of inflammatory cytokines. The present trial is the first analyzing the effectiveness of an OR intervention for gait training in patients with MS. It will help clarify the applicability of robotic technologies to clinical practice, extending the functionality and quality of life of people with MS to face a successful aging process. (ACTRN12619000014156; https://anzctr.org.au/Trial/Registration/TrialReview.aspx?id=376548).

## Introduction

Multiple sclerosis (MS) is a patchy, inflammatory, autoimmune, and demyelination disorder of the central nervous system characterized by the accumulation of progressive neurological impairment (1). MS presents with a wide range of neurological symptoms related to the varying degree and location of axonal and neuronal damage. The disease can follow a variety of clinical courses and is unpredictable in terms of prognosis. Reduced mobility and gait dysfunction are the most noticeable signs of MS; up to 85% of people with MS report difficulty in walking (2, 3) after 10 years of disease onset. In addition, over 60% of people with MS experience some degree of cognitive impairment (4) that correlates with peripheral changes in pro-inflammatory cytokines such as interleukin 1β (IL-1β) and tumor necrosis factor α (5). Fatigue and postural control impairment also appear ubiquitous over the course of MS (6). Increasing evidence suggests that impaired mobility and symptoms such as fatigue are important factors contributing to the observed reduction in quality of life (7) and, in some cases, increased costs (8) associated with MS. In fact, from mid-life and on, MS disease progression can negatively impact employment and participation in everyday activities (9).

An observational study (10) conducted in Canada reported a rise in the prevalence of MS from 1984 - 1997 specifically among people in older age groups. This occurred with minimal changes in the incidence, possibly indicating that patients with MS were living longer. The same trend was also observed in other epidemiological studies conducted in Europe (11–13). As they age, people with MS are at increased risk for developing comorbidities (14–16), at a time when they are often experiencing a progression in their disability (17). Older adults with MS experience limitations in daily-life activities, report low health-related quality of life status, and express concerns about the continuous loss of function and mobility with aging (18–21). People aging with MS also report lower freedom perception relative to that of their cohort peers and fear that they may become a burden on family members (22). In summary, people living with MS are confronted with the challenge of dealing with the functional deterioration associated with disease progression while simultaneously dealing with age-related changes. The resulting decline in functional capacity frequently occurs at a very young age, leading to approach it as a premature aging process.

People with MS perceive gait as one of the most valuable physical functions (23), and consequently regard impaired walking ability as a major physical problem (24). Accordingly, it is of utmost importance to preserve MS patient's capacity to locomote as long as possible to allow for successful aging. Rehabilitation strategies for MS gait dysfunction have experienced significant improvement in recent years and have incorporated new technologies (25). For example, robot-assisted gait training (RAGT), which has shown to be feasible in patients with spinal cord injuries (26) and stroke (27), has also been evaluated in MS (28). RAGT consists on a training modality in which the patient's body weight is supported by a harness while walking on a treadmill with the help of a robotic-driven gait orthosis (29). Morone et al. (30) have identified the following characteristics of RAGT devices: i) capable of mobility with different levels of autonomy, ii) could be classified as either “exoskeletons” (when the movement of specific joints is controlled [i.e. hip, knee or ankle joint]) or “end-effect robots” (the device is at the end of the limb, [i.e. the feet are placed on a footplate]) and iii) could be classified as static (when the patient remains in a fixed environment) or dynamic (if the device enables to change the location). RAGT allows therapists to facilitate the task-oriented practice of walking (31), which potentially leads to learning-dependent neuroplasticity (32). RAGT allows intensive gait training without highly demanding therapists and patients, particularly when treating patients with severe gait impairments.

However, RAGT does not appear to be superior to intensive overground walking training in people with MS. In a recently published randomized controlled study of seventy-two patients affected by severe disability (EDSS 6-7), the effects of 4 weeks of RAGT intervention was compared with conventional walking training in terms of gait speed (33). Both therapies were found to significantly improve gait speed with respect to baseline assessment, but the study failed to demonstrate group by time interactions. Similar improvements were observed for most of the secondary outcomes: walking, endurance, balance, fatigue, and quality of life. However, the improvements obtained during the interventions were lost within a few months of program cessation. Additional studies evaluating RAGT interventions in people with MS and severe walking disabilities (28, 34–37) have yielded similar results. Thus, there is a clear need to understand how best to create stable adaptations that can support and improve the long-term mobility of patients with MS.

The overground robotic exoskeleton (OR) is a relatively new advanced technical device being incorporated into the field of gait rehabilitation. ORs are wearable powered exoskeletons that allow individuals to walk on hard and flat surfaces in a real-world setting. They require a patient's active participation and provide greater motor control stimulation and enriched multisensory information (visual, proprioceptive, tactile, and vestibular) than the RAGT systems (38). Preliminary findings suggest that OR-assisted gait training may be more beneficial than conventional walking training in post-stroke patients (39). A recent study of forty patients with hemiparesis due to stroke compared the effectiveness of OR and conventional gait training in the chronic recovery phase (40). OR gait training resulted in a significant improvement in gait speed, coordination of muscle activations, and frontoparietal effective connectivity. Additionally, recent systematic reviews indicate that OR is a feasible treatment for patients with spinal cord injury (SCI), allowing safe ambulation in real-world environments (41, 42). However, the effectiveness of OR gait training interventions for improving mobility in people with MS has not yet been studied.

Therefore, this study aims to determine the effects of the addition of an OR intervention to the conventional rehabilitation program on gait speed in people with MS and moderate to severe walking disabilities. As a secondary aim, the study will determine the effects of the intervention from a multidimensional perspective, taking into account physical, cognitive and clinical parameters, fatigue and health-related quality of life of the participants. Additionally, as MS is accompanied or mediated by neuro-inflammation, training interventions may stimulate an anti-inflammatory response contributing to the positive effects of exercise in patients with MS (43, 44). Thus, the influence of the intervention on peripheral inflammatory cytokines will also be analyzed. Finally, this study aims to ascertain if the effects of the intervention are maintained over a follow-up period of 3 months.

## Materials and Methods

### Study Design and Participants

This is a prospective parallel-assignment, single-blinded, randomized controlled study. Participants will be randomly assigned to one of the following groups: the control group (CG) or the OR group. The study will take place at the Asociación de Esclerosis Múltiple de Bizkaia (ADEMBI) between January 2019 and December 2019. The assessments will be conducted by blinded research staff at baseline (T1) and after 3 months of training (T2). After a 3-month follow-up period, a final assessment will be performed at 6 months (T3). The study has been designed and results will be reported according to the CONSORT Statement extension for trials of non-pharmacological interventions and pragmatic intervention trials (Figure 1

**Figure 1 F1:**
[figure not shown]
Flow diagram of the study.

). This study was approved by the Ethics Committee of Clinical Research of Euskadi (CEIm) (Code PS2018017) and by the Ethics Committee for Research with Biological Agents of the University of the Basque Country (CEIAB) (Code M30/2018/073).

### Inclusion and Exclusion Criteria, Recruitment, and Randomization

Subjects will be considered eligible for the study if they fulfill all of the following criteria: (a) aged ≥ 18 years, (b) diagnosis of MS according to McDonald criteria (45), (c) moderate to severe gait impairments defined by an Expanded Disability Status Scale (EDSS) score ranging from 4.5 to 7 (46), and (d) the need for one or two canes or crutches for walking outdoors.

Participants will be excluded if they (a) have a neurological pathology in addition to MS, (b) have some musculoskeletal disorder that could limit the extension of the hip and knee or the plantar flexion of the ankle, (c) have suffered an outbreak of MS during the 3 months prior to the start of the study, (d) are under non-stable pharmacological treatment or with treatments expected to be modified during the study, or (e) have received treatment with botulinum toxin in the 12 weeks prior to the beginning of the study.

Recruitment will be done at ADEMBI. Informative meetings will be organized to provide detailed oral and written information about the study, including objectives, studied variables, and methodology, to both potential participants and their families. Participants will sign, indicating informed consent, after fully understanding the study. Using a coin-tossing sequence generation, participants will be randomly allocated at a 1:1 ratio to either the control group (CG) or the intervention group (OR). The assignment will be conveyed via sealed opaque envelopes.

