### Sample Size Calculation

Sample size has been calculated to detect a clinically meaningful change in gait speed: accepting an alpha risk of 0.05 and a beta risk of 0.20 in a bilateral contrast, 32 subjects are required to detect a difference equal to or greater than 0.1 m/sec speed in the 10 meters timed walking test (SD = 0.16). Sample size has been increased an additional 12% to account for losses during follow-up. The resulting sample size is 36 subjects, therefore 18 individuals per group (intervention and control group).

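### Unrestricted coin tossing does not deliver the stated 18 per group, and no step in allocation protects balance on EDSS

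*Protocol article*

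**What the plan says.** Under Inclusion and Exclusion Criteria, Recruitment, and Randomization, the protocol article states: "Using a coin-tossing sequence generation, participants will be randomly allocated at a 1:1 ratio". On concealment it adds: "The assignment will be conveyed via sealed opaque envelopes". No block, stratum, minimisation factor or other restriction is named.

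The Sample Size Calculation section starts from 32 participants ("32 subjects are required to detect a difference equal to or greater than 0.1 m/sec speed"), adds an allowance ("Sample size has been increased an additional 12% to account for losses during follow-up") and concludes: "The resulting sample size is 36 subjects, therefore 18 individuals per group (intervention and control group".

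Eligibility admits an "Expanded Disability Status Scale (EDSS) score ranging from 4.5 to 7" and requires one or two canes or crutches outdoors. Statistical Considerations adjusts for baseline measurements but does not name EDSS. Study Design and Participants describes one centre, blinded assessors and a January to December 2019 window. Trial Status says the trial is already running.

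**The concern.** A fair coin tossed for each participant is simple randomisation. It fixes the probability of each arm at one half but does not fix the group sizes. The method in one section therefore does not produce the group size in another, unless tosses were restricted in a way the article does not describe.

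Two things are at stake:

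- **Group size.** The allowance for losses is four people, two per arm, so an uneven split can use it up before anyone drops out. If equal groups were instead enforced by giving everyone left to the unfilled arm, the final allocations would be known to anyone keeping count. At a single centre where the treating therapists know the arm, that is a practical possibility, and opaque envelopes do not prevent it.
- **Severity.** EDSS is the article's own definition of moderate to severe gait impairment, and the primary outcome is gait speed. Nothing in the allocation balances EDSS, and with 36 people chance differences can be visible.

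**Working it through.** **Inputs.** N = 36, 18 per group, 32 before losses, 12% allowance (Sample Size Calculation). Coin tossing at 1:1 with no restriction named, EDSS 4.5 to 7 (Inclusion and Exclusion Criteria, Recruitment, and Randomization).

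**1. The plan's own figure.** 32 × 1.12 = 35.84, rounded to 36, and 36 / 2 = 18. The last step divides the total by two; it is not a property of the coin. (The 32 itself does not follow from the stated inputs. Two-sided 0.05, 80% power, 0.1 m/s and SD 0.16 give 2 × (1.960 + 0.842)² × 0.16² / 0.1² = 40.2, so 41 per arm. That is a separate matter, and step 3 is therefore shown for two SDs.)

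**2. Group sizes under tossing.** The number in one arm is Binomial(36, 0.5). P(18:18) = C(36,18) / 2³⁶ = 0.132. For k below 18, P(k : 36−k or worse) = 2 × P(X ≤ k). Relative efficiency is 4·n₁·n₂ / 36², and effective N is 36 times that.

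| Split or worse | Probability | Effective N at that split | Efficiency |
|---|---|---|---|
| 16:20 | 61.8% | 35.6 | 98.8% |
| 15:21 | 40.5% | 35.0 | 97.2% |
| 14:22 | 24.3% | 34.2 | 95.1% |
| 12:24 | 6.5% | 32.0 | 88.9% |

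The smaller arm starts below 16 (half of 32) in 40.5% of sequences, before any dropout. In terms of precision the allowance is fully used only at 12:24, where effective N falls to 32.

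**3. Power.** Power (normal approximation) is Φ(0.1 / [SD × √(1/n₁ + 1/n₂)] − 1.96), averaged over the binomial split:

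- SD 0.16 (stated): 46.6% at fixed 18:18, 45.6% on average under tossing.
- SD 0.10 (about the value that would give 16 per arm): 85.1% and 84.0%.

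The loss is about 1 point either way. Average efficiency is 1 − 36/36² = 97.2%, because the squared difference in group size has expectation 36.

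**4. If 18:18 were forced by stopping when one arm fills.** The expected number of determined allocations is 36 × C(36,18) / 2³⁶ = 36 × 0.132 = 4.8.

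**5. EDSS imbalance.** The article gives no EDSS distribution, so assume that exactly 18 of 36 are in an upper band and the arms are 18:18. The upper-band count in one arm is hypergeometric: P(x) = C(18,x)·C(18,18−x) / C(36,18). The between-arm difference is |2x − 18| / 18, in steps of 11.1 points, so at least 25 points means |x − 9| ≥ 3. The probability is 9.4%.

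For a gap of at least 20 points, with 30% to 50% in the upper band, the probability is 15% to 32% at fixed 18:18 and about 24% under coin tossing. The two methods carry a similar risk.

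**The case against.** The strongest reply is that 18 per group sits in the sample-size section and reads as a planning target, curable by the word expected. Simple randomisation is valid, and it is less predictable than small blocks. The average cost is about 1 point of power. All of this stands, and it limits the weight of the point. It does not make the two sections consistent, and a reader cannot tell whether tosses were ever overridden.

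For the primary outcome, the planned ANCOVA adjusts for baseline gait speed, which measures directly the feature that makes EDSS relevant, and the walking-aid criterion narrows the range. This also stands in part. The article does not show that baseline speed carries all the prognostic information in EDSS, and the Friedman alternative it names would not adjust for anything.

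Stronger readings are tempting but not supported:

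- A reader might infer that the coin biases the comparison or seriously cuts power. Steps 2 and 3 show otherwise.
- A reader might blame the coin for EDSS imbalance. Step 5 shows that the cause is the absence of stratification, since a fixed 18:18 split carries a similar risk.
- Treating the arms as two independent Binomial(18, 0.5) samples gives 13.2% for a 25-point gap. That does not match the premise that exactly half the sample is in the upper band; 9.4% does.
- A reader might say a tossed sequence cannot be audited. It cannot be regenerated from a seed, but a written record and retained envelopes can be checked, and nothing says they were not kept.
- Nothing in the article shows that tosses were in fact overridden.

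**Conclusion.** The point holds as a moderate one. The stated method yields the stated 18 per group in about 13% of sequences. It leaves the smaller arm below 16 in about 40%, and it gives 12:24 or worse in 6.5%. The validity of the comparison is not in question and the average power loss is about 1 point; the exposure is to an unlucky split, or to predictable final allocations if equality was enforced. These figures assume independent fair tosses for all 36 participants, as the article literally describes.

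The EDSS limb is separate and is a risk, not a certainty: about 9% for a gap of at least 25 percentage points at 18:18. It rests on the assumption that half the sample is in the upper band. Adjustment for baseline gait speed reduces its effect only partly.

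**What to change.** **Allocations not yet made.** Use a computer-generated permuted-block list with varying block sizes, optionally stratified by two EDSS bands. Someone outside recruitment should prepare it, and it should be kept in the opaque envelopes already planned.

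**Whatever has been allocated.**

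- Add baseline EDSS, already collected for eligibility, as a covariate in the primary gait-speed ANCOVA.
- Restate 18 per group as an expected size for the part randomised by coin.
- Report the achieved numbers per arm and whether any toss was overridden.

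**Cost.** A short amendment and one degree of freedom. Blocks are slightly more predictable than pure tossing. Blocks may also end incomplete, particularly within strata, so the result is near-equal groups and not a guaranteed 18:18. With six months per participant and a planned finish in December 2019, enrolment has to close by about mid-2019, so the new list may reach few participants or none. The covariate and the reporting changes remain available regardless.

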### Control Group Intervention (CG)

Subjects in the CG will participate in the routine physiotherapy sessions provided to all patients with MS at ADEMBI. ADEMBI is a reference MS center for providing expertise and specialized rehabilitation to people with MS, where all the participants receive individualized assistance throughout the year following the latest recommendations and clinical guidelines for managing the disease. The duration of each session is one hour; in these sessions, conventional methods of physiotherapy are provided to control spasticity, maintain articular range and exercise balance.

### Overground Robotic Gait Training Group (OR)

Subjects in the intervention group will receive the same physiotherapy treatments scheduled for the control group and will participate in 3 months of individualized and progressive gait training assisted by an OR (Ekso^TM^, Ekso Bionics, USA). Ekso^TM^ is a powered, wearable exoskeleton with actuated hips and knees that provides assistance to lower limb segments during movement. The gait training program's technical content is based on a literature review, author's expertise, and field experience (Table 1). It has been designed taking into account the multi-modal training approach, as has been recommended by expert physical therapists on the rehabilitation of patients with MS (47), to allow the “far transfer effect”. This effect refers to the occurrence of transferring the improved performance from a specific function to different untrained functional domains (48). Interventions will be individually supervised by experienced physiotherapists properly trained in Ekso^TM^ driving and will consist of twice weekly sessions assisted by the wearable exoskeleton in two modalities: 1) *PreGait*: to exercise static balance and weight shifts at the beginning of each session; 2) *ProStepPlus:* to gait train, with steps triggered by the user's lateral weight shift. Subjects will wear their own shoes and orthotics during the training sessions. The parameters (duration, speed, cadence, length of the steps, robotic assistance, etc.) of the intervention will be adapted to each participant, and the duration of the training sessions progressively increased as participants increase their tolerance, aiming to achieve 20-40 minutes of OR training (including the exoskeleton donning and doffing) by the end of the 3 month training period. The session will end with 10 minutes of cryotherapy on knee extensors and ankle plantar flexors. There will be at least 48 hours between training sessions, and goals will be adapted in response to illness, injury, or physical symptoms.

**Table 1 T1:** Technical content of the OR gait training program.

***PreGait***	2–3 exercises of static weight shift in progressive difficulty to identify:		
	(a) Symmetric distribution of weight		
	(b) A given lateral weight displacement point		
	**1st Month**	**2nd Month**	**3rd Month**
	Patients assisted by acoustic stimuli	Reduction of external stimuli and lateral weight displacement point	Lateral weight displacement and step on the site
*ProStepPlus*	Gait training sessions of progressive length and difficulty according to patient tolerance (maximum 40 min/session)		
	**1st Month**	**2nd Month**	**3rd Month**
	Patients assisted by acoustic stimuli when reaching the lateral point to trigger the step	Reduction of external stimuli and lateral weight displacement point trigger	Increase the duration and speed of the sessions targeting a functional gait
	Ekso^TM^ bilateral full adaptive assistance	Ekso^TM^ bilateral full adaptive assistance	Ekso^TM^ bilateral full adaptive assistance
Cryotherapy	10 min on knee extensors and ankle plantar flexors in a supine position.		

